## Abstract

**Background:**

Occupational exposure to tuberculosis (TB) constitutes a major health risk for healthcare workers (HCWs). The HIV epidemic equally affects the workforce because of the mutually reinforcing epidemiology of HIV and TB. Stigmas associated with HIV and TB have become so intricately entangled that they stop some HCWs from seeking care in a context where serious shortages in human resources for health besiege public health facilities. It is thus imperative to research, as well as attempt to tackle, HIV and TB stigma among HCWs. But little has been done internationally—and nationally, only our own exploratory studies. Our project aims to address this by (1) scientifically assessing the extent and sources of HIV and TB-related stigma among HCWs and (2) developing and testing evidence-based, stigma-reduction interventions in public hospitals in the Free State Province of South Africa.

**Methods/design:**

The research follows a stratified cluster randomised controlled trial (RCT) design. Pre intervention, a self-administered questionnaire with the pilot study’s validated stigma scales is used to measure stigma and other key variables among randomly selected HCWs in eight hospitals—stratified by size and district and then randomly allocated to four intervention and four control sites. Interventions comprise HIV- and TB-stigma reduction activities—mainly Social and Behavioural Change Communication (SBCC) interventions—at three social-ecology levels (individual, community, and socio-structural). An outside assessor will appraise the trial mid-way through implementation. Post intervention, all baseline respondents will be followed up to complete the baseline questionnaire with additional items on interventions. Qualitative data will be collected to better understand HIV and TB stigma and explore if, and how, interventions impact stigma levels in the workplace.

**Discussion:**

The study regards as HCWs *all* staff, working in *all* different types of jobs, at *all* levels in the hospitals. Thus, the research addresses HIV and TB stigma across the whole workforce and the entire workplace. In doing so it will (1) generate essential information on stigma among HCWs and (2) implement stigma-reduction interventions that are innovative yet replicable, and potentially beneficial in addressing a pernicious human-rights-based issue.

**Trial registration:**

South African National Clinical Trials Register, registration ID: DOH-27-1115-5204. Prospectively registered on 26 August 2015.

**Electronic supplementary material:**

The online version of this article (10.1186/s13063-018-2713-5) contains supplementary material, which is available to authorized users.

## Background (Standard Protocol Items: Recommendations for Interventional Trials (SPIRIT) point 6a)

Stigma is a Greek word for a mark that was cut or burned into the skin—it identified people as criminals, slaves, or traitors to be shunned. In his seminal work Erving Goffman [1] drew on this age-old notion to define stigma as an attribute, quality, or association that significantly discredits an individual in the eyes of others. He proposed that people who do not conform to socially sanctioned norms resort to acts of concealment to protect themselves and to manage others’ impressions of them. More recent HIV literature [2–5] emphasises stigma as a *process* that involves differentiation, othering, and discrimination. Two main forms of stigma emerge: external and internal. External stigma manifests as negative attitudes and beliefs that lead people to reject, avoid, or fear those who they think have an undesirable ‘mark’ such as HIV or TB. Internal stigma refers to beliefs that a person holds about himself or herself—negative *self*-*judgements* based on that person’s lived experience, but sometimes based purely on observations of how society treats *others* with the same or similar undesirable ‘mark’. We focus on stigma because it attacks a person’s self-worth, affects a person’s right to dignity, and thus violates human rights.

We focus on HIV *and* TB stigma because of the mutually reinforcing epidemiology of the two diseases, which has led to a devastating HIV-TB co-epidemic in South Africa. HIV prevalence is high: in 2016 an estimated 18.9% South African adults aged 15–49 years were HIV-infected, with an even higher estimate of 29.7% among women in antenatal care [6]. TB in South Africa is also high, with an estimated 450,000 cases of active TB in 2013 [7].The gravity of the co-epidemic is seen in the HIV prevalence in TB incident cases in South Africa—estimated to be as high as 57% [8]. Even though the two diseases are very different—for instance, TB is airborne and curable, while HIV is predominantly sexually transmitted and incurable—people rightfully associate the two diseases because so many people with HIV die of TB. An unfortunate consequence of this is that the *stigmas* associated with the two diseases have also become intricately entangled in people’s minds and actions.

As occurs in the general population, stigma stops some HCWs from seeking care for TB and HIV [9]. Reluctance to seek help must be seen in tandem with serious shortages in human resources for health in South Africa’s public health facilities—we cannot afford absenteeism, long sick leave, or worse, attrition in our healthcare workforce. Reluctance to seek help must also be seen against a backdrop of risk. Risk of HIV infection among HCWs is likely to be similar to the general population: approximately 18.9% are HIV-infected [6]. HCWs’ risk of contracting TB is nearly four times more than the general population [10] and they may be six times more likely to be hospitalised for drug-resistant (DR) TB than the population that they care for [11]. The epidemiological realities of HIV and TB, together with HIV and TB stigma and discrimination act as ‘key barriers to both the delivery of quality health services by health providers and to their utilisation by community members and health providers themselves’ [12]. These are compelling reasons for researching HIV and TB stigma among HCWs and for developing and testing workplace interventions to reduce stigma.

Because there are so few scientific tools, particularly validated tools, to measure stigma in the public healthcare setting, it has been difficult to evaluate the success or failure of stigma-reduction interventions. This was noted by Uys et al. [9] who indicated that the majority of papers reporting stigma intervention outcomes lacked a validated instrument to measure change in stigma over time. There are several differences between our study and the limited number of others that investigate stigma in healthcare facilities. Some focus only on HIV (and not on HIV and TB) as in the case of the Nyblade et al. [12] tool for measuring stigma among health facility staff. Most focussed almost exclusively on stigmatising attitudes of HCWs towards patients and not on stigmatisation among HCWs themselves. Finally, our research spans the entire healthcare workforce and workplace, unlike other studies that measure stigma in a limited sub-set of healthcare professionals and/or workstations [13–16]. Thus, there are gaps in past and current research that indicate a clear need for reliable and validated scales to measure both HIV and TB stigma across the entire healthcare workforce and workplace.

Based on a solid theoretical framework, and our findings from a series of small preliminary studies [17, 18], the current proposal team Research Centre for Longitudinal & Life Course Studies-Centre for Health Systems Research & Development (CHSR&D-CELLO) worked closely together in 2012–2013 to develop and refine a range of scales to measure the most important dimensions of TB and HIV stigma: external and internal stigma [19, 20]. External stigma is directed by HCWs *outwards* towards other HCWs, and internal stigma is directed by HCWs *inwards* towards themselves. The resulting parallel scales—measuring external and internal stigma towards HIV *and* TB—were piloted in Pelonomi Regional Hospital (Free State, South Africa; Stigma Score Pilot Study; ethical clearance: ECUFS NR 192/2012). Subsequently the pilot stigma scales were validated and the results published in *Clinical Infectious Diseases* [21].

At the same time that the Stigma Score Pilot Study was being conducted, insights from an academic literature review on stigma-reduction interventions, particularly in healthcare settings, were used to inform workshops with key stakeholders, out of which a series of stigma-reduction interventions designed to work at different socio-ecological levels (individual, community, and structural) were proposed and discussed. The work of Li et al. on HIV stigma among healthcare workers (HCWs) in China [22–24] strongly influenced our decision to apply the theory of the Diffusion of Innovations [25] to intervention design. The theory recommends the deployment of change agents—or as Li et al. call them, popular opinion leaders—to promote socio-behavioural change. Results of their trial involving 1760 service providers in 40 hospitals in China found that hospitals delivering HIV-related stigma-reduction interventions reported more desirable intervention outcomes than those in control hospitals [26]. Raising awareness of HIV and TB stigma is quite common in wider societal- and community-level contexts in South Africa. Among the myriad and mixed results of such efforts are indications that communication interventions can have an adverse effect, and *increase* stigma [27]. Nonetheless, it seems more often the case that stigma-reduction campaigns across different media and communication platforms are beneficial, at least to some degree (cf. [28, 29]). The Social and Behavioural Change Communication (SBCC) intervention design we finally decided on combines the Diffusion of Innovations change agent/popular opinion leader approach with a social marketing campaign that promotes a locally relevant, culturally sensitive slogan and image targeting all HCWs with a single stigma-reduction message. The initial research on interventions and our piloted imagery were subsequently published in *Global Public Health* [30].

To the best of our knowledge—as informed by a comprehensive review of available academic literature—ours are the first research studies conducted on HIV and TB stigma among HCWs in South African healthcare facilities. Without having first established the extent and sources of HIV and TB stigma in the South African healthcare workforce, it would be premature to conduct research that compares this phenomenon in South Africa with what occurs in other countries or regions. Therefore, for our current randomised controlled trial (RCT) we chose as comparators eight randomly selected public hospitals (four intervention vs four control) situated in the same province of South Africa—the Free State (SPIRIT point 6b). This choice is sound in terms of the number of possible comparators (27 hospitals) as well as in terms of geography and expertise. The *Centre for Health Systems Research & Development (CHSR&D)* is situated at the University of the Free State (UFS) in Bloemfontein, in the middle of the province. The CHSR&D was established 25 years ago in the Faculty of the Humanities and has considerable expertise, as well as working partnerships, built over decades of research in the province’s public health facilities. The University of Antwerp (AU), Faculty of Political and Social Sciences, Department of Sociology, *Research Centre for Longitudinal & Life Course Studies (CELLO)* has a very long history of fruitful research partnership with the CHSR&D and also has excellent working knowledge of public health in the province.

In response to the research needs outlined above, as well as to extend the preliminary work of our *Stigma Score Pilot Study*, the CHSR&D and CELLO designed a randomised control trial with two key objectives (SPIRIT point 7) in mind: (1) to measure stigma by scientifically assessing the extent and sources of HIV and TB stigmatisation among the healthcare workforce and (2) to design, refine and test evidence-based, stigma-reduction interventions in randomly selected public hospitals in the Free State Province of South Africa.

This article presents the protocol for the RCT, and is written to comply with the recommended SPIRIT guidelines for RCT protocols [31] (Additional file 1).

## Methods/design

### Trial design (SPIRIT point 8)

The research follows a stratified cluster RCT design. Pre intervention, a self-administered questionnaire with the pilot study’s validated stigma scales was used to measure stigma and other key variables among randomly selected HCWs in all eight randomly selected sites. The intervention comprises of stigma reduction activities at three social-ecology levels (individual, community, and structural) in the four intervention sites. To evaluate implementation, an outside assessor will appraise the trial mid-way through its implementation, partly by collecting qualitative data from purposively selected HCWs. Post intervention, all respondents from baseline will be followed up using the same scales with added questions on interventions. Quantitative and qualitative data will be collected to assess the size of the impact as well as to uncover the processes through which the interventions may impact on stigmatisation.

### Study setting and site selection (SPIRIT point 9)

The study settings are public hospitals in the Free State Province, South Africa. From the total population of 28 hospitals that could be selected as comparators, one was eliminated (Pelonomi Regional Hospital) because it was the site of the Stigma Score Pilot Study.

In order to ensure an equal distribution of large and small hospitals across the different districts in both intervention and control arms, hospitals of similar size (based on numbers of staff), and where possible in the same district, were deliberately paired. Within these pairs, a coin toss was used to randomly allocate hospitals to Arm A or Arm B, and then again to allocate the two arms to intervention or control. The number of hospitals required was estimated considering the fact that the number of staff members across the hospitals in each group differ. The average number of staff members per hospital considered is 220. The same parameters were used as those used to calculate the sample (described later), and the number of hospitals required was estimated to be approximately four hospitals per group (intervention / control). A full list of the sites appears in the addenda (Additional file 2).

### Participants

The study regards as HCWs *all* staff, working in *all* different types of jobs, at *all* levels in the hospitals. Thus, we are measuring stigma and intervening across the whole workforce and the entire workplace.

#### Sampling (SPIRIT point 14)

The parameters used for sample size calculation were estimated from the Stigma Score Pilot Study. The mean stigma score considered for the control group was 0.85 with a standard deviation of 0.71. The stigma score is expected to be reduced by approximately 24% to 0.65 in the intervention group with a standard deviation of 0.39. The two-tailed test is considered with Type I error of 0.05 and Type II error of 0.10, to give 90% power. The coefficient of variation considered for each group is 0.25 and the intra-cluster correlation coefficient is 0.05. The estimated sample size per arm is 173 and the estimated inflation factor (design effect) is 1.7. Therefore, the required sample size for this study per arm is approximately 173 × 1.7 ≈ 292 participants. The total number of participants required for this study is 584 (347 respondents in intervention sites and 237 in control sites).

The same HCWs participate in baseline and the post-intervention surveys. Based on our extensive experience of fieldwork in Free State hospitals [32], we estimate that the baseline survey will need 50% oversampling of respondents to allow for loss-to-follow up between baseline and post-intervention surveys (SPIRIT point 15). In practice, a random sample of 882 HCWs was drawn from three broad job categories: *healthcare professionals* (446) (physicians, nurses, and allied HCWs such as psychologists, pharmacists, etc.); *management and administrative staff* (116); and *support staff* (318) (e.g. messengers, cleaners, porters, housekeeping, catering, security, etc.). Two respondents did not indicate their job category.

For the baseline and follow-up survey components of the study a sampling frame (SPIRIT point 16a) for individual respondents (and replacements) was drawn up for each hospital site using its most recent, up-to-date database of employees. Employees were allocated to the following three occupational groups: (1) clinical professionals (including physicians, nurses, and allied healthcare professionals such as physiotherapists, occupational therapists, speech therapists, dieticians, pharmacists, social workers, radiographers, etc.); (2) management and administrative staff (e.g. chief executive officer (CEO), finance officers, clerks, etc.) and (3) support staff (e.g. household aids, messengers, porters, etc.). We sampled participants from each occupational group proportionally to the overall size of the groups *in each hospital*. Random sampling was used to select participants for inclusion into the study. For each occupational group, this entailed arranging names alphabetically and using Excel 2010 to randomly assign numbers to each staff name. The random numbers and corresponding staff names were then arranged in ascending order before selecting the required number of staff within each occupational group. All remaining staff on the list were considered as replacements in the case of refusals and staff not being available. Replacement staff names were selected in ascending order of appearance of the random numbers. In total, 24.0% of HCWs were not able to participate (no longer working there, unavailable, refusal) and had to be replaced.

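### The sample size attributes every parameter to a one-hospital scale pilot, which cannot give a between-hospital ICC and is not shown to have an intervention group; the stated 90% power depends on the unsupported intervention-arm SD of 0.39

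*Protocol article*

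**What the plan says.** The Sampling section opens with an unqualified attribution: "The parameters used for sample size calculation were estimated from the Stigma Score Pilot Study". The values follow. For the control arm, "The mean stigma score considered for the control group was 0.85 with a standard deviation of 0.71". For the intervention arm, the score is expected to be "reduced by approximately 24% to 0.65 in the intervention group with a standard deviation of 0.39". The error rates are given as "The two-tailed test is considered with Type I error of 0.05 and Type II error of 0.10, to give 90% power". A CV of 0.25 for each group and an ICC of 0.05 come next, and no source is named for any value other than the pilot. The section reaches 173 per arm before clustering, applies a design effect of 1.7, and arrives at 292 per arm, 584 in total, split 347 intervention and 237 control. The site selection section says that the number of hospitals was set from the same parameters.

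The Background describes the pilot. Its scales "were piloted in Pelonomi Regional Hospital (Free State, South Africa; Stigma Score Pilot Study". Of the interventions it says: "At the same time that the Stigma Score Pilot Study was being conducted", literature and stakeholder workshops were used, in which "interventions designed to work at different socio-ecological levels (individual, community, and structural) were proposed and discussed". The site selection section confirms a single pilot site: "one was eliminated (Pelonomi Regional Hospital) because it was the site of the Stigma Score Pilot Study".

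**The concern.** The stated source and the description of that source do not fit together. An ICC for a trial that randomises hospitals needs variation between hospitals, and a study in one hospital contains none. An SD under intervention needs people who have received one. The article describes the pilot as a test of scales, carried out while interventions were still at the workshop stage.

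The SD matters most for the stated figure. A lower mean may well bring a lower SD. But 0.39 against 0.71 is a fall of 1 − 0.39/0.71 = 45% in SD, or 1 − 0.1521/0.5041 = 70% in variance, beside a fall of 0.20/0.85 = 24% in the mean. No reason is given for so large a reduction. If 0.39 is a planning value, the 90% power is conditional on it, and a reader told that it is a pilot estimate has no cause to question it. This affects how a null result would be read.

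**Working it through.** **Inputs** (all from the Sampling section): means 0.85 and 0.65, so the difference is 0.20; SDs 0.71 and 0.39; two-sided alpha 0.05; power 90%; design effect 1.7; 292 per arm. Four hospitals per arm comes from the site selection section.

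**Step 1: the plan's own figure.** n per arm = (z₀.₉₇₅ + z₀.₉₀)² × (SD₁² + SD₂²)/difference², with (1.960 + 1.282)² = 10.507.

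10.507 × (0.5041 + 0.1521)/0.04 = 172.4, rounded up to 173. The stated figure reproduces. (173 × 1.7 = 294 and 172 × 1.7 = 292.4, so the stated 292 is a matter of rounding.)

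**Step 2: vary only the intervention SD.** If the SD falls in proportion to the mean, it is 0.71 × 0.65/0.85 = 0.543.

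- SD 0.543: 10.507 × (0.5041 + 0.2948)/0.04 = 209.9, so 210 per arm before clustering.
- SD 0.71: 10.507 × (2 × 0.5041)/0.04 = 264.8, so 265 per arm before clustering, or 265 × 1.7 = 450.5 after it, against 292 planned.

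**Step 3: power at the planned size.** Effective n per arm = 292/1.7 = 171.8. Power = Φ(0.20/√[(0.71² + SD₂²)/171.8] − 1.960). For the stated split, the variance is 1.7 × (0.71²/237 + SD₂²/347).

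| Intervention SD | 0.20/standard error, 292 per arm | Power, 292 per arm | Power, 347/237 split |
|---|---|---|---|
| 0.39 (plan) | 3.236 | 90% | 86% |
| 0.543 (proportional) | 2.938 | 84% | 80% |
| 0.71 (same as control) | 2.610 | 74% | 73% |

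**Step 4: why these are nominal.** They accept the design effect of 1.7. With 292/4 = 73 respondents per hospital and ICC 0.05, the usual formula gives 1 + (73 − 1) × 0.05 = 4.6. A value of 1.7 with that ICC would need 1 + 0.7/0.05 = 15 respondents per hospital. At 4.6 the effective n is 292/4.6 = 63.5, and power by the same formula is about 50%, 43% and 35% for the three SDs, before any correction for having only eight hospitals.

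**Step 5: which values the described pilot could supply.**

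- Control mean and SD: yes, from a survey of staff in one hospital.
- ICC between hospitals: no.
- Intervention SD: not unless the pilot had an intervention group, and none is mentioned.
- CV: cannot be judged. It is not defined, and could refer to hospital means or to hospital sizes. If sizes, staffing records could supply it, since the site selection section refers to differing staff numbers and an average of 220.

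**The case against.** The case on the other side has several parts.

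- **The wording signals planning values.** The intervention mean is introduced as expected, and the control mean and the CV as considered. One may read the pilot as the source of 0.85 and 0.71 only. That is a fair reading of intent, and it makes concealment too strong a charge. It does not cure the opening sentence, which covers all the parameters; labelling them separately would.
- **The absence of an intervention group is an inference.** The article never says so outright. It mentions piloted imagery, pilot training sessions and piloted interventions, though it ties none of them to the Stigma Score Pilot Study or to stigma scores. The pilot publication and the full protocol are not shown and might give a source. This stands, so the claim is that the SD appears unsupported, not that it is proven to be invented.
- **Equal SDs of 0.71 are the cautious end.** If the score has a floor at zero (an assumption), a mean of 0.85 with SD 0.71 suggests right skew, and an intervention that trims the upper tail would reduce the SD. This stands: 74% is one end of a range.
- **The design may recover power.** The same staff are measured twice and a linear mixed model is planned. With baseline adjustment and an assumed baseline-to-follow-up correlation r, the ratio 2.610 is divided by √(1 − r²). Power with SD 0.71 in both arms then becomes 78%, 85% or 90% for r = 0.3, 0.5 or 0.6. If all 882 sampled staff were retained (441 per arm), it would be 89% without adjustment. Both figures keep the design effect at 1.7. The possibility is real, but the stated 90% claims neither source of precision and no correlation is given.

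A reader might also infer that the stated ICC of 0.05 drives the 90%. It does not: Step 4 shows that the value is not carried into a design effect of 1.7 at the planned cluster size. Its missing source is a matter of provenance, separate from the SD effect.

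**Conclusion.** The concern holds as a fault of provenance with a material effect on the stated power. The pilot as described cannot have supplied the ICC and very probably did not supply the intervention SD; the source of the CV is unclear. The 173 per arm and the 90% depend on the SD of 0.39. Over the range 0.39 to 0.71, nominal power at 292 per arm runs from 90% to 74%, or from 86% to 73% with the stated split.

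These figures assume a normal test, a difference of 0.20, the plan's design effect of 1.7 and no gain from baseline adjustment. It would be tempting to conclude that the trial's true power is 74%, or that the SD is the main reason power may fall short. The documents support neither. The SD of 0.71 under intervention is a scenario, and the mismatch between the ICC and the design effect moves power further than the SD does (90% to about 50% with SD 0.39 kept).

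**What to change.** In the Sampling section:

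1. Say which parameters came from the pilot. Label the intervention SD, the ICC and the CV as assumptions unless a source is given, and define the CV.
2. Restate power with SD 0.71, or the SD from the collected baseline, in both arms as the conservative case, and show the range down to 0.39 as sensitivity.
3. Use a design effect that agrees with the stated ICC and the respondents per hospital. If credit is taken for baseline adjustment, state the assumed correlation.
4. Report the ICC from the eight-hospital baseline with its confidence interval. It will be wide: for illustration, an estimate of 0.05 with about 110 respondents per hospital (882/8) has a 95% interval of roughly 0.017 to 0.20. It therefore informs the range of power but does not settle it.

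The baseline data are already collected, so the cost is a short recalculation. Enrolment need not change. The price is a less favourable stated power.

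### The coefficient of variation of 0.25 is undefined beside the ICC of 0.05, and on either reading four hospitals per arm do not give the stated 90% power in the plan's own unadjusted calculation

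*Protocol article*

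**What the plan says.** The inputs are in the protocol article, Sampling (SPIRIT point 14). For the control group: "The mean stigma score considered for the control group was 0.85 with a standard deviation of 0.71". The score is expected to be "reduced by approximately 24% to 0.65 in the intervention group with a standard deviation of 0.39". The error rates follow: "The two-tailed test is considered with Type I error of 0.05 and Type II error of 0.10, to give 90% power". Clustering enters through one sentence: "The coefficient of variation considered for each group is 0.25 and the intra-cluster correlation coefficient is 0.05". The result is "The estimated sample size per arm is 173 and the estimated inflation factor (design effect) is 1.7", and then "the required sample size for this study per arm is approximately 173 × 1.7 ≈ 292 participants". The total is 584, split as 347 in intervention sites and 237 in control sites.

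The section on study setting and site selection (SPIRIT point 9) covers the number of hospitals. It notes that staff numbers differ between the hospitals of a group, takes an average of 220 staff per hospital, and arrives at approximately four hospitals per group. On the inputs it says: "The same parameters were used as those used to calculate the sample (described later". The Background gives the pool as the "number of possible comparators (27 hospitals" in the province.

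**The concern.** With eight hospitals, the between-hospital variance largely decides what the trial can show. A between-hospital CV of the outcome and an ICC are two ways of stating that variance: once the mean and SD are fixed, one determines the other. The plan gives both a CV and an ICC and does not say what the CV describes. A reader therefore cannot tell whether the plan assumes one between-hospital variance or two.

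In addition, the stated design effect of 1.7 has to fit the design actually chosen, which is four hospitals per arm. If it does not, the 90% power is unsupported whatever the CV means, and a null result could be read as evidence of no effect when the trial had limited power to show one.

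**Working it through.** **Inputs** (Sampling section unless noted): means 0.85 and 0.65, difference 0.20; SDs 0.71 and 0.39; two-sided 5%, 90% power; CV 0.25; ICC 0.05; design effect 1.7; 292 per arm. Four hospitals per arm comes from the site-selection section. The average number of respondents per hospital is 292/4 = 73.

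**1. The plan's own figures.**
- Sum of variances: 0.71² + 0.39² = 0.6562. With (1.960 + 1.282)² = 10.507, n per arm = 10.507 × 0.6562 / 0.20² = 172.4, rounded up to 173. This reproduces.
- 173 × 1.7 = 294.1, against the stated 292; 172 × 1.7 = 292.4. The difference is rounding.
- With design effect 1.7: SE = √(0.6562 × 1.7 / 292) = 0.0618, ratio 0.20/0.0618 = 3.24, normal power 90%. So the stated power follows if 1.7 is right.

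**2. What 0.25 could be.**
- It is not the CV of individual scores: 0.71/0.85 = 0.84 and 0.39/0.65 = 0.60.
- *Between-hospital CV of the score.* Between-hospital SDs are 0.25 × 0.85 = 0.2125 and 0.25 × 0.65 = 0.1625. If the stated SDs are total SDs, the ICCs are 0.2125²/0.71² = 0.090 and 0.1625²/0.39² = 0.174. If they are within-hospital SDs, the ICCs are 0.2125²/(0.2125² + 0.71²) = 0.082 and 0.1625²/(0.1625² + 0.39²) = 0.148. Conversely, ICC 0.05 corresponds to CVs of √0.05 × 0.71/0.85 = 0.187 and √0.05 × 0.39/0.65 = 0.134. The two inputs conflict on this reading.
- *CV of hospital size.* It then says nothing about the ICC and both figures can stand. It enters the design effect as 1 + ((1 + CV²)m − 1) × ICC.

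**3. Does 1.7 fit four hospitals per arm?**
- At ICC 0.05, 1 + (m − 1) × 0.05 = 1.7 needs m = 15 respondents per hospital, or m = 14.1 with a size CV of 0.25.
- At the actual m = 73: 1 + 72 × 0.05 = 4.6. With a size CV of 0.25: 1 + (1.0625 × 73 − 1) × 0.05 = 4.83.

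**4. Power for a difference of 0.20, four hospitals and 292 respondents per arm.** The comparison is unpaired and uses no baseline measurement. The t column uses 6 df, for 4 + 4 hospitals.

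| Assumption | SE | Normal | t, 6 df |
|---|---|---|---|
| ICC 0.05, design effect 4.6 | 0.102 | 50% | 38% |
| ICC 0.05, size CV 0.25, design effect 4.83 | 0.104 | 48% | 37% |
| Between-hospital CV 0.25 (total SDs) | 0.141 | 29% | 22% |

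For the last row, the between-hospital variances sum to 0.0625 × (0.85² + 0.65²) = 0.0716, so SE = √((0.6562 − 0.0716)/292 + 0.0716/4) = 0.141. With the planned 347/237 split, the ICC 0.05 row is 49% or 37% and the last row is again 29% or 22%.

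**5. Would more staff per hospital help?** With unlimited respondents at ICC 0.05, SE = √(0.05 × 0.6562/4) = 0.0906, and power is at most 60% (normal) or 46% (t, 6 df). With a between-hospital CV of 0.25, SE = √(0.0716/4) = 0.134, and the ceiling is 32% or 24%.

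**The case against.** The tempting stronger reading is that the two inputs contradict each other outright. The document does not support that. It never calls 0.25 the between-hospital CV of the score. The site-selection section speaks of staff numbers that differ between the hospitals of each group, so a CV of hospital size is at least as plausible. With that reading and m = 14, the design effect is 1.694 and 172.37 × 1.694 = 292.0, the stated sample size. This does not prove the reading, because m = 15 with no CV also gives 1.7, but it shows the figures are compatible with it. The full protocol, which is not shown here, may define the term.

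This objection stands and makes the conflict conditional. It does not rescue the power: the match to 1.7 needs about 14 respondents per hospital, and the design has 73.

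A second objection is that the power loss at ICC 0.05 comes from the cluster size behind 1.7 and not from the CV. That is correct. Defining the CV alone would not restore 90%.

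A third is that the calculation ignores the pairing of hospitals by size and, where possible, district, and the follow-up of the same staff with a mixed model of change. Between-hospital variance in change may be smaller than in level. This also stands. It is therefore too strong to say that four hospitals per arm cannot reach 90% power under any analysis. However, the Sampling section claims no such gain, and its 173 and 1.7 come from the unadjusted comparison.

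**Conclusion.** The point holds in conditional form. The CV of 0.25 is undefined in the article. If it describes the stigma score between hospitals, it implies ICCs of about 0.09 and 0.17 (0.08 and 0.15 if the SDs are within-hospital) and cannot stand beside 0.05. If it describes hospital size, the two inputs are compatible.

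On either reading, the stated 90% is not supported by the plan's own unadjusted calculation with four hospitals and about 292 respondents per arm. Power is about 48–50% (normal) or 37–38% (t, 6 df) at ICC 0.05, and about 29% or 22% if 0.25 is the between-hospital CV of the score. These figures assume the plan's means and SDs, equal respondents per hospital except where a size CV is used, and no credit for pairing or baseline. They do not show what the planned mixed model will achieve.

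The ICC also needs a better source. The Sampling section attributes its parameters to the pilot study, which the Background places in one hospital, and one hospital carries no information on variance between hospitals.

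**What to change.** In the Sampling section:

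- State what the CV of 0.25 refers to.
- If it is the between-hospital CV of the score, keep one between-hospital variance and remove the other figure. If it is the CV of hospital size, use 1 + ((1 + CV²)m − 1) × ICC with the actual number of respondents per hospital.
- Estimate the between-hospital variance of the score, with its interval, from the eight-hospital baseline survey already collected.
- From that one value, restate the power for a difference of 0.20, or the detectable difference, for four hospitals per arm. State explicitly any gain claimed from pairing and from baseline adjustment, and the assumption behind it.
- Make the site-selection section, which relies on the same parameters, agree with the result.

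The cost is a short recalculation and a few sentences. Enrolment does not change. The stated power is likely to become less favourable.
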